#### Phase II feasibility and potential effectiveness evaluation

A comparative hybrid type II feasibility/potential effectiveness implementation trial will be designed and conducted for evaluating at least one active de-implementation strategy defined through the phase I formative mixed research compared with the usual procedures of dissemination of clinical practice guidelines (e.g., “what-not-to-do” guidelines), focused on the provision of materials, support tools, and training (reference group). A mixed-methods evaluation will be undertaken: quantitative for assessing the results of implementation at the professional level (process and implementation outcomes regarding reductions in low-value pharmacological prescribing and the adoption, reach and implementation of the recommended clinical practice in CVD primary prevention) and qualitative for assessing the feasibility and perceived impact of the de-implementation strategy from the clinicians’ perspective and ascertaining the experience and satisfaction of patients concerning the clinical care received. The unit of intervention will be the PC physician, while observation and analysis will be performed at professional and patient levels. Thus, the trial will tentatively be randomized at the level of PC physician with at least two intervention arms (dissemination vs. de-implementation strategy). The diffusion of the final design of the planned evaluation is warranted.

### Participants

(i) Professionals: Osakidetza PC physicians willing to be involved in a process focused on the optimization of CVD primary prevention; and (ii) patients: all women aged 45–74 years and men aged 40–74 years with hypercholesterolemia but without diagnosed ischemic heart or cardiovascular disease and with a low estimated CVD Risk (< 5%) according to REGICOR who attend at least one appointment at the collaborating PC practices during the study period. Informed consent of PC physicians as representatives of the clusters will be obtained prior to trial commencement.

### Comparison de-implementation strategies

The active comparator will be passive dissemination, defined as a set of usual procedures for the dissemination of clinical practice guidelines (“what-not-to-do” guidelines) focused on the diffusion of knowledge and abilities mainly through the provision of materials, support tools, and training. This control intervention will be compared with at least one active experimental de-implementation strategy, emerging from the formative research, defined by a set of de-implementation strategies targeting the facilitators of the non-desired behavior (seeking to suppress it), while tackling the barriers to and encouraging the preferred/desired behavior. This experimental de-implementation intervention could tentatively be broken down into several distinct de-implementation strategies to be compared to the control intervention.

### Randomization

The FPs will be randomly assigned to one of at least two study arms, using a random number sequence generated by computer prior to the start of the trial: one of the groups will be exposed to the de-implementation strategy that emerges from the systematic process of identifying determinants and mapping tailored interventions established by the BCW; and the other the usual procedures for disseminating clinical practice guidelines (“what-not-to-do” recommendations) focused on the provision of materials, support tools, and training. The allocation sequence will be generated using a specifically restricted scheme by one member of the research team using PROC PLAN/alternatives. The sequence will be concealed at the coordination center. The physician will be allocated only after they have given written informed consent. The random assignment in a tentative three-arm design will be similar. Given that the strategy is an optimization of services or clinical care already offered in Osakidetza, participants are expected to be blind to the allocation group. The data analyst and the personnel in charge of measurements will be blind to physician allocation to study arms.

### Outcome measures

To assess the feasibility/potential effectiveness of compared de-implementation strategies in terms of public health significance, we will use the Reach, Efficacy, Adoption, Implementation, and Maintenance (RE-AIM) framework [41].

#### Reach

Percentage of eligible patients (low-risk patients with hypercholesterolemia but without ischemic heart or cardiovascular disease) ascribed to collaborating FP who received the recommended CVD primary prevention practice as dictated by the CVD Prevention Clinical Practice Guideline [13], this being the health promotion intervention action (e.g., assessment of advice regarding healthy lifestyles), 12 months after exposure of the FP to the compared de-implementation strategies

#### Effectiveness

Changes observed in attitudes towards health promotion and perceived ability of physicians to provide a health promotion intervention considered the recommended practice for the primary prevention of CVD in low-risk patients, measured through the Preventative Activity Questionnaire [42]

Changes observed in two clinical and behavioral indicators in a random sample of eligible patients by comparison group exposed to CVD primary prevention actions that emerge from the compared de-implementation strategies, stratified by age and sex. Specifically, a sample of 180 exposed patients will be selected, 15 patients per stratum (2 sex strata, 3 age strata, 2 de-implementation strategies). The use of the aforementioned sampling scheme reflects the intention to maximize the comparability of the populations of exposed users.

As an objective clinical measurement, the change in the REGICOR estimate 12 months after the exposure to the CVD prevention intervention.

As a subjective measurement, the self-reported changes in lifestyle (physical activity, diet, and smoking) 12 months after the intervention, measured through the “prescribe healthy life” (PVS) questionnaire [43], operationalized as (i) proportion of people who have achieved the recommended levels of physical activity (150 min/week of moderate physical activity or 75 min/week of intense physical activity), healthy diet (5 portions/day of fruits and vegetables), and smoking cessation, among those who did not meet these recommended levels on entry into the study; and (ii) weekly minutes dedicated to physical activity of at least moderate intensity, daily number of fruit, and vegetable servings.

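### REGICOR and lifestyle change are compared between arms only in patients who received a prevention action, so randomisation does not protect that contrast

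*Protocol article*

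**What the plan says.** The randomised unit is the primary care physician: "the trial will tentatively be randomized at the level of PC physician with at least two intervention arms" (Phase II feasibility and potential effectiveness evaluation; the Randomization section agrees).

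For the two patient-level indicators, the Effectiveness section defines the population by what the patient received: "in a random sample of eligible patients by comparison group exposed to CVD primary prevention actions that emerge from the compared de-implementation strategies". It then fixes the size and strata: "a sample of 180 exposed patients will be selected, 15 patients per stratum (2 sex strata, 3 age strata, 2 de-implementation strategies". The stated reason is that the scheme "reflects the intention to maximize the comparability of the populations of exposed users". The objective indicator is "the change in the REGICOR estimate 12 months after the exposure to the CVD prevention intervention", and lifestyle change is also measured 12 months after the intervention. The Reach, Adoption, Implementation and Maintenance sections count time from the physician's exposure instead.

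Receipt of prevention actions is itself an outcome. Reach is the share of eligible patients "who received the recommended CVD primary prevention practice as dictated by the CVD Prevention Clinical Practice Guideline", and the second main indicator under Implementation is the incidence of lifestyle advice. The second aim includes raising delivery of lifestyle promotion.

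The Analysis section plans intention-to-treat for the primary statin outcome and mixed models adjusted for potential confounders. It carries a similar approach over to secondary outcomes.

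**The concern.** Restricting the comparison to exposed patients conditions on an event that follows randomisation and that the strategies aim to alter. If dissemination physicians advise a few selected patients and active-arm physicians advise many, the exposed patients in the two arms may differ in motivation or baseline lifestyle before any effect of the strategy. Random sampling within the exposed reproduces that selection faithfully. A difference in REGICOR or lifestyle change could then be read as an effect of the strategy when part or all of it reflects who was advised.

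**Working it through.** **1. The plan's own figure.** 15 patients × 2 sexes × 3 age groups × 2 strategies = 180, so 90 per arm. The figure reproduces. The issue is the sampling frame, not this count.

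**2. What exposed means here.** Three features of the Effectiveness section point to the patient's receipt of a prevention action rather than to the physician's allocation: the sample is of eligible patients exposed to actions that arise from the strategies, the scheme refers to exposed users, and the 12-month clock starts at the prevention intervention. A between-arm comparison is implied by sampling per strategy, by the aim of comparability, and by the analysis planned for secondary outcomes.

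**3. Can selection alone produce a difference?** The article gives no exposure rates, so every input in this step is an assumption. Take two patient types within an age-sex stratum, half motivated and half not. Motivated patients gain 60 min/week of activity and the others gain 0, in both arms, so there is no true effect. With exposure probabilities p_m (motivated) and p_u (unmotivated), the share motivated among the exposed is 0.5·p_m / (0.5·p_m + 0.5·p_u) = p_m / (p_m + p_u).

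| Control p_m / p_u | Active p_m / p_u | Motivated among exposed, control vs active | Spurious difference (active − control) |
|---|---|---|---|
| 20% / 10% | 50% / 40% | 66.7% vs 55.6% | −6.7 min/week |
| 20% / 5% | 60% / 50% | 80.0% vs 54.5% | −15.3 min/week |
| 30% / 5% | 80% / 70% | 85.7% vs 53.3% | −19.4 min/week |
| 20% / 10% | 20% / 10% | 66.7% vs 66.7% | 0 |
| 20% / 5% | 60% / 15% | 80.0% vs 80.0% | 0 |
| 5% / 20% | 50% / 60% | 20.0% vs 45.5% | +15.3 min/week |

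The bias vanishes if each type is exposed equally in both arms, or if the strategy multiplies exposure by the same factor in both types. It changes sign if less motivated patients are advised first (last row). Because it arises within strata, 15 patients per age-sex cell does not remove it.

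**4. Size relative to precision, under a strong assumption.** Suppose physicians advise strictly from the top of one normally distributed trait: 20% of patients in control, 40% to 60% in the active arm. The trait means among the exposed are 1.40 (top 20%), 0.97 (top 40%) and 0.64 (top 60%), so the arms differ by 0.43 to 0.76 SD. With an assumed trait-outcome correlation of 0.1 to 0.3:

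- lower end: 0.43 × 0.1 = 0.04 SD
- upper end: 0.76 × 0.3 = 0.23 SD
- standard error for 90 vs 90, ignoring clustering: √(2/90) = 0.149 SD
- ratio: about 0.3 to 1.5 standard errors

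Strict ranking is an extreme case. Any randomness in who is advised shrinks these figures, and clustering would enlarge the standard error.

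**5. What sampling all eligible patients would cost in precision.** Assume receipt of an action shifts the outcome by 0.5 SD in both arms, with the exposure rates of step 4. The contrast becomes (0.40 − 0.20) × 0.5 = 0.10 SD to (0.60 − 0.20) × 0.5 = 0.20 SD. Against a standard error of 0.149, two-sided power at 5% is roughly 10% to 27%.

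**The case against.** The strongest reply is that RE-AIM separates how many patients are reached from what happens to those reached. Reach and the incidence of lifestyle advice are already assessed in the eligible population, so the Effectiveness indicators need not carry the benefit of reaching more people. That stands: the exposed-only sample is no gap in that respect, and it is a sensible way to describe recipients within an arm.

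It is also true that the plan offers more than age-sex balance, since the Analysis section foresees confounder adjustment for secondary outcomes. That helps with recorded variables. It does not restore a randomised comparison on motivation or on the physician's selectivity.

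Third, these are two indicators in one RE-AIM dimension of a feasibility and potential-effectiveness evaluation. The trial design is called tentative, and no sample-size justification or hypothesis test is stated for them. This limits the consequence but does not remove the flaw.

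A reader might infer that the exposed groups are in fact not comparable, or that the control arm would be favoured. The documents support neither. With no exposure rates given, the bias may be zero and its sign depends on who is advised first. Eligibility is also confined to an estimated risk below 5%, which limits how far the groups can differ in risk.

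**Conclusion.** The point holds in this form: the between-arm contrast in REGICOR and lifestyle change conditions on a post-randomisation event that the strategies aim to change, so its comparability is not protected by randomisation. Neither the stratification nor the planned adjustment repairs this. No size can be derived from the article. The illustrations, from zero to about 0.23 SD or about 1.5 standard errors, rest wholly on assumed exposure rates, assumed selection and assumed correlations. The primary statin outcome is planned by intention-to-treat in the target population and is not touched. What changes is the claim these patient-level results can support: description of recipients, not an effect of the strategy.

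**What to change.** **Minimum change.** State in the Effectiveness section that REGICOR and lifestyle results in exposed patients will be reported descriptively within each arm, labelled as a non-randomised comparison, with no between-arm effectiveness claim. This needs no new data and no change to the 180 patients. The cost is giving up a causal reading that the design does not support.

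**If a between-arm effect on these outcomes is wanted.** Draw the age-sex stratified sample from all eligible patients of the randomised physicians, regardless of whether they received a prevention action. Count time from the physician's exposure. Analyse by the physician's arm, allowing for clustering, and weight for the equal-cell sampling so that the estimate refers to the eligible population.

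The costs are real and should be stated. At 180 patients the diluted contrast will be imprecise (roughly 10% to 27% power under the assumptions in the working). Unadvised patients must also be contacted for the questionnaire, including at entry to identify those not meeting the recommended levels. The Phase II section foresees publication of the final design, so either change can still be made there.

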#### Adoption

Percentage of FPs out of the total addressed to participate that collaborate in a process to optimize CVD primary prevention practice; characteristics of those participating/not-participating.

Percentage of FPs who change their CVD prevention practice by reducing low-value statin prescribing and increasing health promotion actions in the target population at risk of receiving CVD prevention, 12 months after exposure of physicians to the compared de-implementation strategies.

#### Implementation (main outcome)

The main outcome measures will compare the incidence of both the pharmacological prescribing of statins and the health promotion actions in patients of the target population at risk of receiving CVD primary prevention care, over the 12 months after exposure of collaborating physicians to the compared de-implementation strategies. Specifically, the two following indicators will be compared:
Incidence of low-value prescriptions of statins in patients with no history of statin prescriptions aged between 40 and 74 years in men and between 45 and 74 years in women, with hypercholesterolemia but without ischemic heart disease/CVD, and with an estimated CVD Risk < 5%, attending during the 12 months after exposure of physicians to the compared implementation strategiesIncidence of advice regarding healthy lifestyles in patients with no history of statin prescriptions aged between 40 and 74 years in men and between 45 and 74 years in women, with hypercholesterolemia but without ischemic heart disease/CVD, and with an estimated CVD Risk < 5%, attending PC consultations during the 12 months after exposure of physicians to the compared implementation strategies.

#### Maintenance

Incidence of low-value pharmacological prescriptions of statins and of advice regarding healthy lifestyles in eligible patients, 36 months after exposure of physicians to the compared implementation strategies

#### Spreading

With the aim of assessing a possible spill-over effect of the compared de-implementation strategies in the optimization on the CVD prevention practice, de-prescribing rates in patients with a low-value prescription of statins prescribed before the exposure of physicians to the de-implementation strategies

### Fidelity and feasibility measures

A complete recording and subsequent description of the execution process of the compared de-implementation strategies by group will be carried out to assess the level of fidelity with which they have been carried out with respect to what has been planned: number and percentage of professionals included among those addressed to participate; description of actions carried out (training, work sessions, etc.) and final duration compared to what was planned; participation of professional collaborators in each action (exposure); assessment of the content and usefulness of the implementation actions received by the clinicians; resources dedicated to the execution of de-implementation strategies: support materials, external resources (e.g., external facilitator); and organizational support resources (release of professionals, coverage of services, etc.). All changes made to the de-implementation strategy will be thoroughly described: what has been modified, how, why, by whom, and at what level of delivery (e.g., comparison group level).

### Management, quality, and safety in data processing

All data related to patient sociodemographic characteristics (age, sex, socioeconomic status, etc.) and the clinical practice of their healthcare professionals (e.g., pharmacological prescribing, heath promotion actions) will be extracted from the electronic health record system of Osakidetza (OSABIDE). The Primary Care Research Unit of Bizkaia is formally authorized to extract and use data from electronic health records for research purposes by the Healthcare Directorate of Osakidetza. The confidentiality of the people included in the study will be safeguarded at all times, in accordance with the provisions of the Spanish Organic Law on Protection of Personal Data (3/2018 December 5th, LOPD).

### Analysis

Frequencies and proportions along with their corresponding 95% confidence intervals (CIs) will be used to describe the prevalence and the incidence of low-value pharmacological prescribing of statins in primary prevention of CVD of PC professionals (2018 prescriptions being used as the reference level). Factors associated with inappropriate prescribing of statins will be analyzed through stratified statistical analysis and fitting linear logistic models. Given the three levels involved (patients, clinicians, and health organizations), the average variability and possible associated factors will be estimated using hierarchical models and models based on Bayesian estimators.

The primary outcome will be the incidence of new inappropriate prescriptions of statins in patients of the target population (hypercholesterolemic patients without past or current CVD and with an estimated 10-year cardiovascular risk < 5%) 12 months after exposure of physicians to the compared de-implementation strategies. Therefore, to evaluate the impact of the alternative de-implementation strategies, the relative risk of receiving an inappropriate prescription of statins in patients in the target population of the experimental intervention over that of patients from the reference/control group will be estimated by intention-to-treat. Change in new inappropriate prescription incidence rates from baseline to those observed 12 months after physicians’ exposure to the de-implementation strategies and the relative risk reduction ratio will be estimated with the corresponding 95% confidence intervals. In order to adjust for potential confounding factors, stratified statistical analyses and logistic models will be used. These models will be extended to generalized mixed-effects models to take into account the hierarchical structure of data (patients nested in physicians and physicians in PC teams or specialized care services), with fixed effects (comparison group, effect of time on outcome indicators, and time-group interaction) and random effects on the intercept and the time slope (for each patient, physician, center, etc.). These models will be adjusted for potential confounding variables, following a “forward” strategy guided by the stratified analyses. A similar analytic strategy will be followed for secondary outcomes. The analyses will be carried out with SAS, Stata, and R.

Based on (i) a baseline incidence of 2.7% of new inappropriate statin prescriptions estimated among the patients of the target population seen in 2018 by physicians with an inadequate prescription incidence > 0% with a minimum cluster size n ≥ 20 patients, (ii) an intra-class correlation coefficient of 0.01, (iii) an average cluster size of 56 patients with a coefficient of variation of 0.43, (iv) α = 0.05 and statistical power of 80%, and (v) a hypothetical reduction in annual inappropriate prescription rates in the intervention group of 1.7% in absolute terms or 63% in relative terms (from 2.7 to 1%), the interventional phase will require two study groups with at least 22 physicians each, i.e., at least 44 PC physicians.

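### The mixed model for the primary outcome puts random intercepts and time slopes on patients, although the event can occur only once per patient, and the primary contrast is not named

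*Protocol article*

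**What the plan says.** The main outcome (Outcome measures, Implementation) is "Incidence of low-value prescriptions of statins in patients with no history of statin prescriptions", counted over the 12 months after physicians are exposed to the strategies.

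The Analysis section names two effect measures for it. The first is the relative risk of an inappropriate prescription, experimental over control, by intention-to-treat. The second is the change in incidence from baseline to 12 months, with a relative risk reduction ratio. Logistic models adjust for confounders and are then extended to generalized mixed models "with fixed effects (comparison group, effect of time on outcome indicators, and time-group interaction") and with "random effects on the intercept and the time slope (for each patient, physician, center, etc".). No sentence says which model term carries the primary effect.

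The sample size paragraph of the same section uses "a baseline incidence of 2.7% of new inappropriate statin prescriptions", a reduction of "1.7% in absolute terms or 63% in relative terms (from 2.7 to 1"%), "an intra-class correlation coefficient of 0.01" and "an average cluster size of 56 patients with a coefficient of variation of 0.43". It arrives at 22 physicians per arm. It has no baseline period and no correlation between years.

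**The concern.** A random intercept and slope for each patient needs repeated outcomes on that patient. Here a patient who is prescribed a statin in the baseline period is no longer statin-naive and leaves the population at risk. Everyone else gives at most one zero followed by one binary value. The data therefore cannot separate patient heterogeneity from the fixed effects. Logistic coefficients are conditional on the random effects, so the reported odds ratio would depend on a variance fixed by the software or by assumption.

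The unnamed primary contrast adds to this. A follow-up comparison and a difference-in-change comparison answer different questions with different precision, and the trial was sized for only one of them.

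**Working it through.** **Inputs.** From the sample size paragraph: incidence 2.7% (control) and 1.0% (experimental), 22 physicians per arm, 56 patients per physician, CV 0.43, ICC 0.01. Assumptions: two periods (baseline and 12 months), 2.7% in both arms at baseline, equal physician list sizes in the two years, and a between-year correlation r of physician effects from 0 to 1.

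**1. What the 22 per arm stands for.** The two-proportion formula for 2.7% v 1.0% at one-sided 0.05 and 80% power gives 776 patients per arm. Then 776 × (1 + 55 × 0.01) / 56 = 776 × 1.55 / 56 = 21.5, so 22. Two-sided 0.05 gives 28 with the CV ignored or 30 with it. Sidedness is not stated and is a separate matter. What counts here is that each version compares follow-up incidence only, with no baseline and no interaction.

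**2. Patient-level identification.** Each arm has two hazards, baseline (h1) and follow-up among those still at risk (h2), so two arms give four. The four fixed effects (intercept, group, time, time-by-group) use all four. Nothing at patient level remains for an intercept variance, a slope variance and their covariance.

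Numerical check, leaving physician effects out. Let e1 = expit(a + s0·u) and e2 = expit(a + b + s0·u + s1·v), with u and v independent standard normal. Then h1 = E[e1] and h2 = E[(1 − e1)·e2] / E[1 − e1]. For each pair of patient SDs (s0, s1), a and b were solved so that the hazards equal 2.7%/2.7% in control and 2.7%/1.0% in experimental. All five pairs fit exactly:

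| Patient SD (intercept, slope) | Interaction odds ratio |
|---|---|
| (0, 0) | 0.364 |
| (1, 0) | 0.355 |
| (1, 1) | 0.341 |
| (2, 0) | 0.322 |
| (2, 2) | 0.256 |

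Because the baseline hazards are equal in the two arms, the conditional 12-month odds ratio (group plus interaction) takes the same five values. The marginal relative risk, 0.010/0.027 = 0.37, is the same in every row.

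**3. Support for physician and centre slopes.** Expected follow-up events are 22 × 56 × 0.027 = 33.3 in control and 22 × 56 × 0.010 = 12.3 in experimental, about 46 in all. Per physician and year this is 56 × 0.027 = 1.5 and 56 × 0.010 = 0.6.

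**4. Variance if the interaction were the primary test (log relative risk).**
- Design effect: 1 + ((1 + 0.43²) × 56 − 1) × 0.01 = 1.654.
- Variance of one arm's log incidence: (1 − p) × 1.654 / (22 × 56 × p), which is 0.0484 at 2.7% and 0.1329 at 1.0%.
- Follow-up contrast: 0.0484 + 0.1329 = 0.181.
- Interaction at r = 0: 0.181 + 2 × 0.0484 = 0.278.
- Covariance of baseline and follow-up within an arm: r × 0.01 × √[(1 − p)(1 − q)/(pq)] × (1 + 0.43²)/22, which is 0.0194r in control and 0.0322r in experimental.
- Interaction variance: 0.278 − 2r(0.0194 + 0.0322) = 0.278 − 0.103r.

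| r (assumed) | Interaction variance | Ratio to follow-up contrast |
|---|---|---|
| 0 | 0.278 | 1.53 |
| 0.5 | 0.226 | 1.25 |
| 0.7 | 0.206 | 1.14 |
| 1.0 | 0.175 | 0.96 |

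**The case against.** The sentence on random effects can be read as a generic template. It ends in an open list, and the section says that a similar strategy covers secondary outcomes, some of which (REGICOR change, minutes of activity) are repeated patient measures for which a patient effect is normal. The Phase II section calls the design tentative, and the final random-effects structure is often left to an analysis plan. This softens the point but does not remove it. The mixed models are introduced as the extension of the primary-outcome models, and the patient level is written in, not left open.

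A reader might infer that the treatment effect is taken from the time-by-group interaction, so that the trial loses power. The text does not say so. It names the between-arm relative risk first, and the same model can give a 12-month contrast as group plus interaction. The loss is conditional on choosing the interaction. It depends on a between-year correlation that the protocol does not give, and it vanishes as that correlation nears 1. A random time slope does presuppose that physician rates do not persist perfectly.

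A reader might also infer that the whole model cannot be fitted. That is too broad. The failure of identification concerns the patient level, while physician and centre terms are estimable in principle. The two-period layout is itself an assumption. With finer time intervals, patient effects would rest on the assumed distribution alone.

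**Conclusion.** The point holds for the patient level: the model as written is wrong for a once-only outcome, and its conditional odds ratio can move from about 0.36 to 0.26 with no change in fit. This rests on two periods and on patients leaving the risk set at their event. Physician and centre random slopes are weakly supported, with about 46 follow-up events, but are not impossible.

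The primary contrast is ambiguous rather than wrongly chosen. Using the interaction would give a variance about 1.0 to 1.5 times that of the contrast used for sizing, for an assumed r from 1 to 0. No single power figure can be attached to this from the protocol, and neither a certain power loss nor a general failure to converge is supported. The matter should be corrected before the analysis is fixed.

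**What to change.** For the incidence outcome:
- remove patient-level random effects and all random time slopes;
- keep random intercepts for physician and for team or centre;
- name the 12-month between-arm relative risk as the primary contrast, adjusted for each physician's pre-randomisation incidence;
- report the change-from-baseline (time-by-group) model, with physician-level effects only, as supportive.

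Patient effects may stay for secondary outcomes that are measured repeatedly on the same person.

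The cost is a change of analysis wording. The baseline incidence comes from the same health records. The phase I extraction covers 2014–2018, so a later pre-randomisation year may need a further extraction. The only loss is that the change analysis becomes supportive.

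### Covariates for the randomised comparison are to be chosen by data-driven forward selection, which can inflate the type I error of the between-arm relative risk at follow-up

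*Protocol article*

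**What the plan says.** The Randomization section states: "The FPs will be randomly assigned to one of at least two study arms". For the primary outcome, the Analysis section gives a relative risk for patients "of the experimental intervention over that of patients from the reference/control group will be estimated by intention-to-treat".

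It then brings in adjustment: "In order to adjust for potential confounding factors, stratified statistical analyses and logistic models will be used". These models are extended to mixed-effects models "with fixed effects (comparison group, effect of time on outcome indicators, and time-group interaction", plus random intercepts and time slopes. The covariate rule comes next: the models are to be adjusted for possible confounders "following a “forward” strategy guided by the stratified analyses". The paragraph ends its modelling plan with "A similar analytic strategy will be followed for secondary outcomes".

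The observational phase I analysis sits in the preceding paragraph. The forward strategy is therefore attached to the models that contain the randomised group effect. The article does not say whether the primary relative risk is the unadjusted estimate or one of the adjusted ones.

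**The concern.** Forward selection uses the trial's outcome data to decide which covariates enter, then reports the last model as though it had been chosen in advance. A covariate associated with the outcome by chance is more likely to be kept. If it is also unbalanced between arms by chance, keeping it moves the group estimate. The standard error reflects neither the search nor the other models that could have been chosen.

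This matters most when there is little information, and here there are at least 44 randomised units and a rare outcome. At stake are the nominal 5% level and the coverage of the 95% interval for the main comparison. The estimate itself would also be tied to whichever covariates happened to enter. Because the same strategy passes to the secondary outcomes, each of them could end up with a different adjustment set.

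Leaving a covariate list to a statistical analysis plan would be unremarkable. Here the article itself commits to a selection rule, and a later plan with a fixed set would have to depart from it.

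**Working it through.** **Inputs (Analysis section, sample-size paragraph).** Control incidence 2.7%; intervention incidence 1%; intra-class correlation 0.01; mean cluster size 56 with coefficient of variation (CV) 0.43; "α = 0.05 and statistical power of 80"%; at least 22 physicians per arm.

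**Step 1. The plan's own 22 per arm.** Patients per arm from the pooled two-proportion formula, n = [z(α)√(2p̄q̄) + z(0.80)√(p₁q₁ + p₂q₂)]² / (p₁ − p₂)², with p̄ = 0.0185 and p₁ − p₂ = 0.017:
- One-sided α = 0.05: n = 776.
- Two-sided α = 0.05: n = 986.

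Design effect: 1 + (56 − 1) × 0.01 = 1.55 ignoring the CV, or 1 + ((1 + 0.43²) × 56 − 1) × 0.01 = 1.6535 with it.
- One-sided: 776 × 1.55 / 56 = 21.5, so 22; with the CV 776 × 1.6535 / 56 = 22.9, so 23.
- Two-sided: 986 × 1.55 / 56 = 27.3, so 28; with the CV 986 × 1.6535 / 56 = 29.1, so 30.

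The stated 22 is matched by one-sided calculations. The article does not state sidedness. That is a separate matter; here 44 is simply the planned minimum.

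**Step 2. Events available.** Patients per arm: 22 × 56 = 1,232.
- Planned effect: 1,232 × 0.027 = 33.3 and 1,232 × 0.01 = 12.3, about 46 in total.
- No effect: 2 × 1,232 × 0.027 = 66.5, about 67. This is the count that applies to type I error.

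**Step 3. Type I error of a follow-up-only between-arm comparison, nominal two-sided 5%.** Null trials were simulated with 44 physicians and the inputs above. The article gives no candidates and no entry rule, so both are assumed.

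(a) Weighted physician-level regression on beta-binomial events, 5 or 10 candidates, none or two of them prognostic, 2,500–3,000 runs per setting:

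| Covariate rule | Type I error |
|---|---|
| Unadjusted | 4.5–5.6% |
| All candidates, fixed in advance | 4.6–6.1% |
| Forward, entry p < 0.05 | 5.2–7.6% |
| Forward, entry p < 0.20 | 5.8–9.4% |
| 10% change in estimate | 5.4–8.6% |

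(b) Logistic models with cluster-robust standard errors and 10 noise physician-level candidates:

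| Runs | Unadjusted | Entry p < 0.05 | Entry p < 0.20 |
|---|---|---|---|
| 1,600 | 5.1% | 7.6% | 10.8% |
| 800 | 6.0% | 9.4% | 11.3% |

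The Monte Carlo standard error is √(0.05 × 0.95 / 1,600) = 0.5 points near 5% with 1,600 runs, and √(0.113 × 0.887 / 800) = 1.1 points at 11.3% with 800 runs. The excess over unadjusted in (b) is 2.5 to 5.7 points.

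**Step 4. The same settings as (b), testing the time-group interaction with baseline and follow-up modelled together:**

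| Runs | Unadjusted | Entry p < 0.05 | Entry p < 0.20 |
|---|---|---|---|
| 1,600 | 4.8% | 4.8% | 4.1% |
| 800 | 3.9% | 3.6% | 3.1% |

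There is no inflation. The contrast is within physician, so main effects of physician-level covariates hardly touch it. The 1,600-run set assumed physician rates that are stable across the two periods.

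**The case against.** The strongest reply is that the planned mixed model contains baseline, follow-up and a time-group term. If that interaction is the primary test, Step 4 shows no inflation. This stands, and it limits the point. It does not remove it, because the Analysis section first states the primary effect as a between-arm relative risk at 12 months and does not say that the interaction replaces it.

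Four stronger readings are tempting, and the document does not support them.

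- **That randomisation leaves nothing to adjust for.** Physicians are randomised, but patients enter by attending after their physician's exposure (Participants; Implementation (main outcome)). Patient mix could therefore differ by arm, and some patient-level adjustment is defensible. That argues for a fixed set, not for selection on outcomes.
- **That inflation is a fact of this plan.** A strategy guided by stratified analyses need not mean p-value entry, and the range starts close to nominal.
- **That the error could reach 8–20%.** The physician-level simulation gives this only if the treatment p-value itself steers selection. Nothing in the article says so, and the Randomization section blinds the data analyst. Blinding guards against steering, but not against selection on the outcome.
- **That residual variance is simply made too small.** This describes ordinary linear regression. In logistic models the effect must come through the between-physician variance or chance correlation of covariates with arm.

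It is also fair that this is a feasibility and potential-effectiveness trial whose design is described as tentative, that 44 is a minimum, and that covariate lists commonly sit in an analysis plan. This lowers the urgency but does not make the stated rule a good one.

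**Conclusion.** The point holds in a limited form. The article commits the models for the randomised comparison to outcome-guided covariate selection, and the resulting intervals and p-values ignore that step. For a between-arm follow-up relative risk, type I error can rise from about 5–6% to roughly 5–11% with up to 10 candidates; covariates fixed in advance keep it nominal within simulation error. For a time-group interaction, physician-level main effects cause no visible inflation. Under either contrast, the adjusted estimate depends on which covariates enter.

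The direction is well supported. The size is not a property of the protocol: it rests on assumed candidates and entry rules, on 44 physicians, and on physician-level or cluster-robust analyses. The full planned mixed model was not simulated.

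**What to change.** Delete the forward-selection sentence and name a short covariate set, fixed before unblinding and without reference to the outcome data:

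- the factors used in the restricted randomisation;
- patient age and sex;
- the physician's pre-randomisation prescribing incidence, only if the primary model is follow-up-only. If the baseline period is already an outcome in the model, adding it as a covariate would use it twice.

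Use the same set for the secondary outcomes. Label any further or data-driven adjustment as a sensitivity analysis.

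The cost is a sentence or two and one decision that the wording forces: whether the primary contrast is the follow-up relative risk or the time-group interaction. No extra data or patients are needed.
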